## Methods

### Trial Design

Patients will be recruited through advertisement in the Tuina clinic of the Third Affiliated Hospital of Henan University of Chinese Medicine, Zhengzhou, China. We will follow the SPIRIT (Standard Protocol Items: Recommendations for Interventional Trials) 2013 statement [16] to guide the reporting and development of our protocol. All eligible participants will be required to sign an informed consent form and will be notified that the trial will not contain any collection of human biological specimens.

### Eligibility Criteria

The inclusion criteria are as follows: (1) met the classification and reporting of KOA, per the 1986 American College of Rheumatology criteria [17]; (2) age between 40 and 70 years; (3) experienced knee pain for ≥3 months; (4) knee pain score is ≥3 on the Numerical Rating Scale (NRS) [18]; and (5) radiologically confirmed KOA (Kellgren and Lawrence [K-L] score of 2 or 3) [19].

### Exclusion Criteria

The exclusion criteria are as follows: (1) knee pain associated with other diseases, (2) the individual has undergone intra-articular injections within the last 6 months, (3) a history of knee surgery, (4) psychiatric disorders or chronic severe or acute organic diseases, (5) bleeding disorders, and (6) magnetic resonance imaging (MRI) contraindications, such as phobias or pacemakers.

### Exit Criteria and Management

Exit criteria are as follows: (1) request by the participant and (2) intratreatment side effects.

### Sample Size

The sample size of 64 patients was planned, based on our previous clinical research [9]. The formula is determined:

wherein *N* refers to the sample size in each group, *σ* represents the SD, *α* represents type I error, *β* represents type II error, 1–*β* represents the test power, and *δ* represents the difference between mean groups.

The pressure pain threshold (PPT) values of the treatment and control groups were 9.53 (1.26) and 9.02 (2.62), respectively. We took *α*=0.05, *β*=0.10, 1–*β*=0.90, set the 2-sided test level *α*=0.05, and found out from the *t*-distribution boundary value table: *u*_α_=1.96, *u*_β_=1.282. In this study, *δ*=0.51, *σ* with the larger SD of 1.36, and an approximate *N* of 29 after substituting the formula. With an estimated drop-off rate of 10%, a total of 64 patients with KOA were needed.

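### The sample-size inputs require about 150 patients per group, not 29: power is about 30% rather than 90%, and the SD used matches neither SD quoted

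*Protocol article*

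**What the plan says.** All the figures are in the Sample Size section under Methods.

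- Earlier results: "The pressure pain threshold (PPT) values of the treatment and control groups were 9.53 (1.26) and 9.02 (2.62), respectively".
- Error rates: alpha 0.05, beta 0.10 and power "0.90, set the 2-sided test level" 0.05, with normal deviates 1.96 and 1.282.
- Difference: 0.51, which equals 9.53 − 9.02.
- SD: the text continues "with the larger SD of 1.36, and an approximate" N "of 29 after substituting the formula".
- N "refers to the sample size in each group", so 29 is a per-group number.
- Loss to follow-up: "With an estimated drop-off rate of 10%, a total of 64 patients with KOA were needed".

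The Randomization section sets 1:1 allocation. The Abstract makes resting-state functional connectivity and voxel-based morphometry the primary outcomes and places PPT among the secondary clinical outcomes.

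**The concern.** There are two separate faults. First, the SD put into the formula is described as the larger of two, yet it equals neither quoted SD, and the larger of those is almost twice as big. Second, the N reported does not follow from the inputs printed beside it, whichever SD is used.

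At stake is how the result will be read. If the 90% figure stands, a non-significant PPT comparison will look like a well-powered negative. If the true difference were 0.51 with SD 1.36, a non-significant result would be the expected outcome, with a chance of about 71% at 29 per group. No other justification of the sample size is given, so the number 64 has no support once this calculation falls.

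**Working it through.** **Inputs** (all from Sample Size): u_α = 1.96, u_β = 1.282, δ = 0.51, σ = 1.36, equal groups, N per group.

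**Formula.** The displayed equation is not legible in the copy at hand, but its terms are all defined in the text. For two independent means the standard form is

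N = 2 (u_α + u_β)² (σ/δ)²

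**The plan's own inputs.** (1.96 + 1.282)² = 3.242² = 10.51, and (1.36/0.51)² = 7.11. So N = 2 × 10.51 × 7.11 = 149.5, or **150 per group**. An exact t calculation gives 151. The plan states 29.

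**Attempts to recover 29:**

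| Variant | N per group |
|---|---|
| SD 1.36, factor 2 left out | 75 |
| SD 1.36, one-sided, 90% power | 122 |
| SD 1.36, two-sided, 80% power | 112 |
| SD 1.36, one-sided, 80% power | 88 |
| SD 1.26 | 129 |
| SD 1.26, factor 2 left out | 65 |
| Root mean square of 1.26 and 2.62 (2.06) | 342 |
| SD 2.62 | 555 |

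Solving the formula backwards for N = 29 with δ = 0.51 gives σ = (0.51/3.242) × √(29/2) = 0.60, an SD that appears nowhere. With σ = 1.36, δ would have to be 1.36 × 3.242 × √(2/29) = 1.16.

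The only expression found near 29 is an invalid one, with the factor 2 dropped and σ/δ left unsquared: 10.51 × 1.36/0.51 = 28.03, which rounds up to 29. This may be how the figure arose, but the finding does not depend on it.

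**Power actually available** (two-sided 5% t test, δ = 0.51, noncentral t). The last column is the standardised difference detectable with 90% power at 29 per group, d = 0.866, multiplied by the SD.

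| SD | Power, 29 per group | Power, 32 per group | Difference detectable with 90% power, 29 per group |
|---|---|---|---|
| 1.26 | 33% | 36% | 1.09 |
| 1.36 | 29% | 31% | 1.18 |
| 2.06 | 15% | 16% | 1.78 |
| 2.62 | 11% | 12% | 2.27 |

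At SD 1.36 the detectable difference is 1.18/0.51 = 2.3 times the one assumed. The 95% confidence interval for the PPT difference would have a half-width of about 0.72, wider than the assumed effect.

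**Dropout step.** 29 × 1.10 = 31.9, so 32 per group and 64 in total, as stated. Dividing by the retained fraction gives 29/0.90 = 32.2, so 33 per group and 66 in total. Conversely, 64 × 0.90/2 = 28.8 per group. This is a discrepancy of one or two patients.

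**The case against.** **PPT is secondary.** The primary outcomes are imaging measures, so an error in a PPT calculation does not by itself show that the primary comparison is underpowered. That is correct and limits the consequence. It does not make the 90% figure true, and the whole sample size rests on PPT.

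**The true SD is unknown.** A statement of 29 to 31% power relies on 1.36, the very number in dispute. That is a fair caution: the figure holds on the protocol's own chosen SD, and the full range over the printed SDs is about 11 to 36%. Every value in that range is far below 90%.

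**A more efficient analysis might reduce the SD.** Adjusting for baseline multiplies the residual SD by √(1 − r²), where r is the correlation between baseline and final PPT. Going from 1.36 to 0.60 needs 1 − r² = (0.599/1.36)² = 0.194, so r of about 0.90. The protocol assumes no such correlation, and Data Analysis of Clinical Outcomes describes t, Mann-Whitney and Wilcoxon tests, not an adjusted model.

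**The dropout method is a common convention.** This is true, and the difference is trivial beside a fivefold error. It is a tidying point only.

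**Recruitment was scheduled to start in December 2023.** The correction does not require more patients, so this is no obstacle.

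**Conclusion.** The concern holds. On the protocol's own inputs the required size is 150 per group, about five times the 29 stated, and power for a difference of 0.51 is about 29% at 29 per group and 31% at 32. If 2.62 is the right SD, the shortfall is about nineteenfold (555/29) and power is 11 to 12%. The most favourable printed SD, 1.26, still gives only 33 to 36%.

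These figures assume a two-sided 5% comparison of two independent means with 1:1 allocation, as the section describes. The document cannot show which of the conflicting SDs is the error, but the conclusion does not depend on settling that. The correction is needed because the protocol's only power claim is false as written; the effect on interpretation is confined to PPT.

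**What to change.** 1. Check the earlier trial's PPT SDs and make the Sample Size section consistent. Whether 2.62, 1.36 or another figure is wrong has to come from that source.
2. Delete the N of 29 and the 90% power claim for a difference of 0.51.
3. State what the planned size delivers, using the reconciled SD. If it is 1.36, suitable wording would be: *With 29 evaluable patients per group, power is about 29% for a PPT difference of 0.51 (SD 1.36, two-sided 5% t test) and 90% for a difference of about 1.18 (d = 0.87).* If it is 2.62, the corresponding figures are about 11% and 2.27.
4. If 64 is kept, give its real basis. Feasibility would be an acceptable reason, but the article does not state it and the sponsor would have to confirm it.
5. Inflate for loss as n/(1 − 0.10).
6. Say that a non-significant PPT result will not be taken as evidence of no effect, and report the difference with its confidence interval.

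The cost is a change of wording and a much less favourable power figure. No extra patients and no change in conduct are needed.

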### Recruitment Strategies and Enrollment

The participants will be recruited between December 2023 and December 2024. Participants will also be recruited through a multi-modal strategy, including dissemination through WeChat and posters at community service centers. Figure 1 presents a flow diagram consisting of recruitment, screening, and randomization. Table 1 presents a schematic overview of our trial designs, conduct, review, and analysis.

**Figure 1 figure1:**
[figure not shown]
Flowchart of the trial. fMRI: functional magnetic resonance imaging; HAMD: Hamilton Depression Scale; NRS: Numerical Rating Scale; PPT: pressure pain threshold; WOMAC: Western Ontario and McMaster Universities Osteoarthritis Index.

**Table 1 table1:** Chart of the trial’s time points.

Research process	Enrollment	Allocation	Beginning	End of the experiment
Eligibility screen	✓			
Demographic variables	✓			
Medical variables	✓			
Allocation		✓		
Consent			✓	
fMRI^a^ scan			✓	✓
PPTs^b^			✓	✓
NRS^c^			✓	✓
HAMD^d^			✓	✓
WOMAC^e^			✓	✓
Adverse events			✓	✓
Working practice record			✓	✓

^a^fMRI: functional magnetic resonance imaging.

^b^PPT: pressure pain threshold.

^c^NRS: Numerical Rating Scale.

^d^HAMD: Hamilton Depression Scale.

^e^WOMAC: Western Ontario and McMaster Universities Osteoarthritis Index.

### Randomization

Independent research staff will use SPSS 25.0 (IBM Corp) to generate a randomly numbered sequence for complete randomization. Participants will be randomly assigned into 1 of 2 groups (ie, health education or Tuina group) and applied in a 1:1 allocation ratio. The random sequence will be sealed by a self-governing research assistant via an opaque envelope that contains information regarding the participant’s allocation.

### Blinding

The outcome evaluators and data statisticians will all be masked to the group assignment to prevent bias.

### Interventions

A panel of 2 clinical medical professionals with an academic background in Tuina and clinical medicine agreed to develop a standard protocol for Tuina and health education. The protocol’s feasibility will be examined to determine whether it is practicable and acceptable and to identify any realistic issues caused by the procedures. Given the nature of the treatment, participants will be informed that the trial will be without harm, compensation, and posttrial care.

Clinical medical professionals with ≥3 years of experience with Tuina will conduct the health education for the participants. Before the trial, clinicians will be trained to ensure standard procedures and compliance with treatment protocol. All participants in the Tuina group will receive three 20-minute sessions a week over a 6-week treatment course. The participants in the health education group will participate in health education sessions lasting 1 hour each (administered once weekly for 6 weeks). The participants are to maintain their dietary habits and regular physical activity throughout the study period. Throughout the trial, they will be informed that they are not permitted to entertain other remedies. To guarantee compliance, all participants are required to register for therapy in a written log.

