**Methods:**

This randomized controlled parallel trial will be conducted at the Tuina Clinic of the Third Affiliated Hospital of Henan University of Chinese Medicine (Zhengzhou, China). Patients with KOA will be randomly assigned (1:1) to 6 weeks of health education or Tuina. All patients in both groups will accept a resting-state functional magnetic resonance scan at the beginning and end of the experiment, and the resting-state functional connectivity and the voxel-based morphometry analysis will be performed to detect the RVM and PAG function and structure changes. The clinical outcome assessments will be (1) the pressure pain thresholds, (2) the Numerical Rating Scale, (3) the Hamilton Depression Scale (HAMD), and (4) the Western Ontario and McMaster Universities Osteoarthritis Index (WOMAC). Considering that this trial is a study of resting-state functional magnetic resonance imaging technology, resting-state functional connectivity and voxel-based morphometry are the primary outcomes, and clinical outcome assessments are secondary outcomes. Adverse events will be documented and assessed throughout. All main analyses will be carried out on the basis of the intention-to-treat principle. The outcome evaluators and data statisticians will be masked to the treatment group assignment to reduce the risk of bias.

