### Clinical Outcome Assessments

Validated pain detectors and questionnaires will be used to assess knee pain, psychological characteristics, and function at the beginning and end of the experiment. The clinical outcome assessments will be (1) the PPTs, (2) the NRS, (3) the Hamilton Depression Scale (HAMD), and (4) the Western Ontario and McMaster Universities Osteoarthritis Index (WOMAC). Additional outcome indices included the adverse events of treatment.

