### Adverse Events of Treatment

All adverse events that may occur throughout the trial will be documented, including the time of occurrence, symptoms of discomfort, particular indications, severity, remedy supplied, time course of the action of amelioration, time of determination, and date of remedy termination.

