### Ethical Considerations

This trial was registered in the Chinese Clinical Trials Registry in 2023 (ChiCTR2300070289). The ethics committee of the Third Affiliated Hospital of Henan University of Chinese Medicine has approved this study protocol (ethics approval number 2022HL-031).

This RCT will adhere to the ethical principles governing biomedical research on human participants and respect fundamental human rights in accordance with international recommendations included in the Declaration of Helsinki and its subsequent revisions.

Participants will be given both written and oral information about why the trial will be conducted, its objectives, the potential risks associated, and the guidelines set out during the monitoring period. If a patient fulfills the inclusion criteria and agrees to enroll in the trial, they will provide written informed consent. Patients are free to withdraw consent and discontinue the trial at any time and for any reason.

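### The protocol has participants told that the trial is free of harm, which cannot be squared with its own promise to tell them the potential risks

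*Protocol article*

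**What the plan says.** The protocol article makes two statements about what participants are told.

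- **Interventions:** the sentence opens with "Given the nature of the treatment" and goes on to say that "participants will be informed that the trial will be without harm, compensation, and posttrial care".
- **Ethical Considerations:** participants receive written and oral information on why the trial is done, "its objectives, the potential risks associated", and the rules for the monitoring period.

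Four other places deal with harm.

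- **Exit Criteria and Management** gives two grounds for leaving: "request by the participant and (2) intratreatment side effects".
- **Adverse Events of Treatment** begins "All adverse events that may occur throughout the trial will be documented". The items to be recorded include symptoms, severity and the remedy given.
- **Clinical Outcome Assessments** adds harms to the outcome list: "Additional outcome indices included the adverse events of treatment".
- **The Methods paragraph of the abstract** says "Adverse events will be documented and assessed throughout".

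**The concern.** An assurance that a trial carries no harm and a disclosure of its potential risks are opposite messages to the same person. If staff or participant material follow the Interventions sentence as printed, people are given an assurance that the rest of the protocol does not support. What is at stake is first the soundness of the information on which consent rests.

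Measurement is a secondary matter. Adverse events are an outcome of this trial, and some of what is recorded, such as symptoms of discomfort, depends on what participants say. Someone told to expect no harm may be slower to mention soreness or distress, or may not link it to the trial.

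**Working it through.** No arithmetic applies. The check is to set the statements side by side and ask whether they can all be followed.

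1. **Interventions against Ethical Considerations.** Both govern the content of the information given to participants. If there are potential risks to disclose, the no-harm assurance is wrong. If there were none, the promised disclosure would be empty. This is the direct conflict, and the point rests on it.

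2. **Interventions against Exit Criteria and Management.** One of only two exit grounds is "intratreatment side effects". A plan may provide for an event that it does not expect, so this is weaker evidence than step 1. Still, an unconditional assurance does not fit a plan that foresees people leaving because of side effects.

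3. **Interventions against the adverse-event text.** Recording events that may occur is compatible with expecting few. It is not compatible with telling participants that there will be none. The abstract and the outcome list confirm that harms are meant to be observed.

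4. **The stated reason.** The sentence justifies itself by the nature of the treatment, but the assurance covers the whole trial. Under Table 1, every participant also has MRI and pressure pain testing at the beginning and at the end. The pressure test continues until the participant feels pain. The stated reason does not reach these procedures.

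5. **Is the sentence qualified elsewhere?** No other section mentions compensation or post-trial care, and none limits or corrects the no-harm wording. The Introduction and Discussion call Tuina safe on earlier evidence. A good safety record is not the same as an assurance of no harm.

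6. **Effect on adverse-event reporting.** The Blinding section names outcome evaluators and statisticians as masked, not participants. The article does not say whether events are found by active questioning or by unprompted report, and it gives no expected event rate. Lower reporting, possibly to a different degree in the two arms, is therefore plausible, but no figure can be derived.

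7. **Effect on the statistical design.** The primary outcomes are resting-state functional connectivity and voxel-based morphometry. The sample size of 64 is built on pressure pain threshold, with a 5% two-sided test and 90% power. Neither the outcomes nor the calculation uses adverse-event data, so nothing there changes.

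**The case against.** The strongest counter-argument is that the sentence is bad English rather than policy. Harm, compensation and post-trial care appear as one coordinated list, and the intended meaning may be that there is no provision for compensation for harm or for care after the trial. The article is garbled in other places; it calls the functional images independent of blood oxygen level, for example. Consent itself is described under Ethical Considerations, where risk disclosure, written consent and free withdrawal are promised under ethics committee approval. On this view one clumsy clause is weak evidence of what anyone is told.

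The alternative meaning is possible and should be conceded as such. It does not remove the point: the printed sentence says something else, no other section corrects it, and the correction would be the same under either reading.

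The objection does succeed against several stronger readings that a reader might infer.

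- **That participants were in fact misinformed, or that consent is invalid.** The consent form and participant scripts are not shown. Only the conflict between two sentences can be demonstrated.
- **That adverse events will be under-reported by some stated amount, or that a low count could support no safety statement at all.** The document gives no event rate, no suppression rate and no method of elicitation. Participants are also in regular contact with staff: three sessions a week in the Tuina arm and one in the control arm.
- **That the lack of compensation or post-trial care contradicts the exit rule or the recording of remedies.** Recording a remedy given during the trial is compatible with both.
- **That the exclusion criteria conflict with the assurance.** Excluding people with bleeding disorders or MRI contraindications says nothing about what those enrolled are told.

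**Conclusion.** The protocol gives two incompatible instructions about what participants are told, one of no harm and one of potential risks, and its exit and adverse-event provisions side with the second. As printed, the instruction covers all 64 planned participants. This conclusion rests only on the article's text and on the assumption that the Interventions sentence could be followed as it stands.

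A possible loss of adverse-event reports is a reasonable secondary worry of unknown size, and it touches an additional outcome only. No error rate, power figure, sample size or primary analysis is affected. The point nevertheless deserves correction rather than a note in passing, because it bears on participant safety and the validity of consent and costs very little to put right.

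**What to change.** Delete the no-harm assurance from the Interventions section and from any participant material that carries it. Make that section consistent with Ethical Considerations, so that the only message about harm is the disclosure of potential risks. State the provisions on compensation and post-trial care in a separate sentence, apart from the risk information, so that the two cannot be run together again. What those provisions should be is for the sponsor and the ethics committee.

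Because enrollment began in December 2023, check whether the material already in use contains the assurance. If it does, the correction should also reach those already enrolled.

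The cost is a wording amendment with notification of the ethics committee. A somewhat higher count of reported adverse events is possible. No change to the design, the sample size or the analyses follows.

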### Tuina Group

The standard Tuina procedure will be performed based on Tuina Therapy, a textbook of the 13th Five-year Plan [20]. The specific administration procedure will first start with the hand disinfection of the Tuina clinical medical professional. Second, the specific application of Tuina will be performed according to the following methods [9]: (1) the participant will be placed supine on the treatment bed, and the Tuina therapist will press at the points Xuehai (SP10), Yinlingquan (SP9), Yanglingquan (GB34), Liangqiu (ST34), Xiyan (EX-LE5), and Zusanli (ST36; based on the standard of the World Health Organization [21]; Figure 2); (2) the participant will be asked to sit in a chair, the knee will be flexed to 90 degrees, and the Tuina therapist will revolve the foot of the participant to a neutral position and lightly press the patella’s lower edge; the therapist’s other fingers will then be wrapped around the knee’s rear without force. The participant will be instructed to stand, and the therapist will push the patella. The participant will then be required to sit down. This process will be repeated 3 times.

